### Economic evaluation and statistical methods

The costs of both therapies will be compared using the Student’s *t* test. Uncertainty over the cost and effectiveness differentials between the two groups will be measured using the bootstrap resampling method. Cost-effectiveness will be measured using the incremental cost-effectiveness ratio per life year gained. Markov modelling will be used to calculate the cost-effectiveness ratio by simulating patient follow-up beyond the end of the study.

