### Trial assessments

The last enrolled patient will be followed up for 12 months after the start of treatment (D0). All other patients will be followed up until the final visit of the last enrolled patient. Patients will therefore be followed up for a maximum of 48 months and a minimum of 12 months following start of treatment. All patients will be assessed by the schedule summarised in Table 2. Treatment will be discontinued if the patient withdraws consent, if the treating physician deems it necessary for medical reasons or if a serious adverse event occurs - after discontinuation, patients should be assessed by CT as soon as possible to assess response to treatment.

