### Outcome definitions

 OS is defined as the time from the date of randomisation to death from any cause. PFS - the time from the date of first treatment to disease progression - and tumour response rate (complete response, partial response, stability, or progression) will be determined from serial CT scans using RECIST, modified RECIST, EASL criteria for HCC, and Choi criteria[21]. Radiological examinations will be conducted by abdominal radiologists at each centre followed by a separate centralised review of radiological examinations. The general and liver disease-specific quality of life scores will be calculated using the European Organisation for Research and Treatment of Cancer (EORTC) quality of life questionnaire (QLQ-C30) version 3 and the HCC-specific QLQ-HCC 18 questionnaire[22]. Adverse events will be reported according to National Cancer Institute criteria (National Cancer Institute Common Terminology criteria for Adverse Events (NCI CTCAE) Version 4.0)[23].

The cost of therapy from the hospital’s perspective will be estimated by including all the resources that are directly attributable to the procedure (that is, equipment, tests, total work time, and so on), which will be assigned a value based on the purchase price by the hospital. The mean overall cost per patient from the payer’s perspective will include the relative stay index and readmissions during the patient’s follow-up period. Calculation of the incremental cost-effectiveness ratio per year of survival or the incremental cost-utility ratio between RE and sorafenib will be complemented by the bootstrap resampling method and an acceptability curve for the cost-effectiveness ratio.

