### Sample size calculation and statistical considerations

Based on OS data with sorafenib from the SHARP study[6] and with yttrium-90 RE reported in the literature[9, 11–15], the number of patients required for randomisation to detect a clinically relevant increase (4 months) in OS time with RE versus sorafenib was determined as 400 patients (200 patients in each treatment arm). This translates to an expected median OS time of 10.7 months in the sorafenib group and 15 months in the RE group, with an accrual period of 24 months and follow-up of 12 months. These guarantee a power of 80% with a bilateral alpha risk of 5%. Estimating that up to 10% of patients that are recruited will not fulfil the criteria of eligibility for randomisation, we aimed to enrol 440 patients.

A Data Monitoring Committee (DMC) will regularly review the toxicity data to assess the safety profile of the treatment (including serious adverse events and mortality). The first intermediate analysis will take place once 30 patients have been followed up for at least 2 months in each treatment arm, after which the DMC will convene every 6 months.

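### The payer cost per patient accrues over unequal, administratively censored follow-up, but costs are compared with a plain Student's t test that treats incomplete totals as final

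*Protocol article*

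**What the plan says.** Four statements in the protocol article combine here.

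- **Test.** Economic evaluation and statistical methods: "The costs of both therapies will be compared using the" Student's t test. Bootstrap resampling is added for uncertainty in the cost and effectiveness differentials.
- **Payer cost.** Outcome definitions says that the overall cost from the payer's "perspective will include the relative stay index and readmissions during the" patient's follow-up. The hospital-perspective cost is separate and is built by "including all the resources that are directly attributable to the procedure".
- **Length of follow-up.** Trial assessments: "Patients will therefore be followed up for a maximum of 48 months and a minimum of 12 months following start of treatment". The last patient is followed for 12 months, and "All other patients will be followed up until the final visit of the last enrolled patient".
- **Cost-effectiveness.** "Cost-effectiveness will be measured using the incremental cost-effectiveness ratio per life year gained", with a Markov model that simulates follow-up past the end of the study.

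Outcome measures lists the average payer cost per patient among the cost endpoints, and cost is a secondary endpoint of the trial.

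**The concern.** A two-sample t test needs one complete value per patient. A patient who dies before close-out supplies one. A patient still alive has spent only part of what the trial would have recorded with longer observation, and how much is missing depends on the date of entry. Averaging these values as if complete estimates a mean over a mixture of follow-up lengths, which corresponds to no stated time horizon.

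The close-out rule is the same in both arms, but the share of incomplete records is not if survival differs, and the trial is designed on the expectation that it does. The timing of cost may differ too: RE is given in one or a few sessions, while sorafenib is a continuing oral treatment. At stake is the payer cost difference, together with any within-trial cost and effect differentials formed from the same totals. The overall survival result is not touched.

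**Working it through.** **Inputs.** From Sample size calculation and statistical considerations: "expected median OS time of 10.7 months in the sorafenib group and 15 months in the RE group", accrual of 24 months, follow-up of 12 months, 80% power, two-sided 5%, 200 per arm. Assumed here: exponential survival and uniform accrual, so that censoring time C is uniform on 12 to 36 months.

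**1. Reproduce the plan's sample size.** The hazard ratio is 10.7/15 = 0.713.
- Schoenfeld events: 4(1.960 + 0.842)²/(ln 0.713)² gives 276.
- Freedman events: (1.960 + 0.842)² × [(1 + 0.713)/(1 − 0.713)]² gives 281.
- The mean event probability (from step 2) is 1 − (0.233 + 0.347)/2 = 0.710.
- N is therefore 389 or 396, within 3% of the stated 400. The model matches the plan's own.

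**2. Share alive at close-out.** With λ = ln 2/median (0.06478 and 0.04621 per month), P(censored) = (e^(−12λ) − e^(−36λ))/(24λ).
- Sorafenib: (0.4596 − 0.0971)/1.5547 = 0.233.
- RE: (0.5744 − 0.1895)/1.1090 = 0.347.

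**3. Observed time against a common 36-month horizon.** Mean observed time is (1 − P(censored))/λ. The restricted mean to 36 months is (1 − e^(−36λ))/λ.

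| | Sorafenib | RE |
|---|---|---|
| Mean observed months | 11.84 | 14.13 |
| Restricted mean, 36 months | 13.94 | 17.54 |
| Months lost | 2.10 | 3.41 |
| Shortfall | 15.1% | 19.4% |

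**4. Sensitivity to the accrual period.** 24 + 12 gives a maximum near 36 months, whereas Trial assessments gives 48; the two passages need reconciling. With 36 months of accrual (48-month maximum), 17.8% and 28.0% are censored, and observed means of 12.69 and 15.58 fall 14.0% and 19.2% short of the 48-month restricted means of 14.75 and 19.29. The picture hardly changes.

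**5. From time to cost.** This step needs cost rates, which the documents do not give. If all cost fell at the start of treatment, nothing would be truncated. If cost accrued at a constant a per month on sorafenib and b per month on RE until death, the raw difference (RE minus sorafenib) would be off by 2.10a − 3.41b. That is positive when b is below 2.10/3.41 = 0.62 of a, and negative when b is above it. Even the sign is therefore open.

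**The case against.** **The article is a summary.** A full protocol or analysis plan may set a horizon and a censoring method, and their absence from the article is no fault. That stands. What the article does fix is a named test and a payer cost defined over the patient's own follow-up, and these two do not fit together.

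**The hospital cost is hardly exposed.** It is confined to resources tied to the procedure. That stands, and the point is limited accordingly.

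**The close-out is common to both arms.** With equal survival, mean observed time would be 11.84 months in each arm. A reader might infer that the result reflects accrual speed rather than the treatments. That goes too far: truncation differs by arm only through differences in survival or in the timing of cost.

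**Life-years and the cost-effectiveness ratio.** A reader might set the observed gain of 14.13 − 11.84 = 2.29 months against the restricted-mean gain of 17.54 − 13.94 = 3.60 and conclude that the ratio's denominator is 36% too small. The documents do not support this. Nowhere do they say that life-years will be the raw mean of observed time. Statistical analysis uses Kaplan-Meier for survival, which handles censoring, and the ratio is to be calculated with a Markov model beyond study end. How the model's inputs treat censoring is not described, so bias there is neither shown nor excluded. The model does not, however, alter the separate t test on cost, and a bootstrap measures sampling uncertainty without removing censoring bias.

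**No cost bias has been computed.** That also stands. RE cost may fall largely up front, and sorafenib may be suspended, reduced or stopped before death, so a constant monthly rate is an illustration only.

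**Conclusion.** The point holds for the payer-perspective mean cost. Followed as written, the t test would treat incomplete costs as final for about 23% of sorafenib and 35% of RE patients, and those patients' observed time is cut short to a different degree in each arm (about 15% and 19% of the 36-month restricted mean). These figures rest on the design medians, exponential survival, uniform 24-month accrual and 12-month minimum follow-up. They are shortfalls in time. They carry over to cost only under a constant monthly rate, and neither the size nor the direction of the bias in the cost difference can be stated from the documents.

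The point does not extend to the hospital procedure cost, nor, on what is written, to the Markov-based ratio. It concerns one component of a secondary endpoint and should be corrected before the economic analysis is run.

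**What to change.** For the payer cost, and for the within-trial cost and effect differentials, replace the t test on follow-up totals with a mean difference over a stated common horizon.

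- **12 months.** Every survivor completes this (withdrawal and loss aside), so a simple mean difference with a bootstrap interval is valid. It should not stand alone, because it drops all later cost.
- **A longer horizon short of maximum follow-up, for example 24 or 30 months.** Use inverse-probability-of-censoring-weighted or interval-partitioned mean cost, with restricted mean survival to the same horizon, re-estimated within each bootstrap sample. The horizon should not be 36 months: under 24 + 12 months the chance of being uncensored at month t is (36 − t)/24, which is 0.50 at 24, 0.25 at 30 and zero at 36, so weights become unbounded there.
- **Markov model.** Use these adjusted estimates as its inputs, and say so.

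The cost is dated cost records, some programming and somewhat wider intervals at the longer horizon. Patients, visits and sample size do not change.

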## Discussion

The SARAH trial will compare the efficacy and safety of RE with that of sorafenib in the treatment of advanced HCC (see Additional file2). To the authors’ knowledge, no prospective, controlled trials have been published, randomised or otherwise, on the efficacy of yttrium-90 RE in patients with HCC.

Sorafenib has been chosen as the control in the SARAH trial as it is the current recommended first-line treatment for advanced (Barcelona stage C) HCC[2, 6, 25]. Median OS is significantly increased by nearly 3 months with sorafenib versus placebo[6, 7]. However, the incidence of adverse events was high (80%) in the SHARP trial and there was no improvement in time to symptomatic progression with sorafenib therapy[6]. Attempts to improve outcomes for patients with advanced HCC on sorafenib by combination with other drug therapies have had limited success when compared with sorafenib alone[26–30]. Sorafenib combination therapy with transarterial chemoembolisation (TACE) has shown promise in patients with unresectable HCC[31], but is not currently recommended for advanced HCC. Indeed, combination therapy with sorafenib is not currently recommended outside the clinical trial setting for advanced HCC[27], and there is a need for an efficacious alternative with a favourable safety profile. RE with yttrium-90 is also indicated as a first-line treatment for unresectable HCC in a number of countries, and is associated with a high response rate in HCC patients (78 to 89% across 14 studies)[8]. Thus a head-to-head, prospective trial of these two treatments warrants investigation.

Some aspects of the SARAH study design are worth further discussion. The inclusion criteria are similar to the SHARP trial, except extrahepatic dissemination is not permitted in the SARAH study as RE is a localised therapy. Although previous treatment for advanced HCC is an exclusion criterion, prior chemoembolisation is permitted as patients failing chemoembolisation would be indicated for sorafenib therapy. Eligible patients in the SARAH study have also been stratified according to ECOG score, as this is an independent prognostic factor for survival in patients with HCC treated with RE or sorafenib[10, 32]. In addition, patients will be stratified by presence or absence of macroscopic vascular involvement as vascular involvement has been associated with poor prognosis in patients with HCC[10, 13, 33].

In the SARAH trial, OS has been chosen as the primary endpoint as it is a more robust measure than PFS, and the SHARP trial demonstrated the efficacy of sorafenib based on this criterion. Moreover, the kinetics of tumour progression, as assessed from imaging techniques, is different between RE and sorafenib, rendering OS the best option for comparison between arms in this trial. An Asian study with similar inclusion criteria has now commenced, which compares sorafenib with RE in patients with locally advanced HCC[34], and could be used for meta-analysis in the future.

In addition to efficacy analyses, the SARAH trial offers the possibility of rigorously confirming the toxicity caused by sorafenib versus RE in patients with advanced HCC. This is important as the cardiovascular toxicity of sorafenib has been highlighted in a meta-analysis of cancer patients (predominantly renal carcinoma)[35], but was not a common complication in the SHARP study[6]. The SARAH trial will also offer the opportunity to conduct ancillary studies (for example, dosimetry and CT perfusion), and compare the cost of each treatment. A definitive economic evaluation of sorafenib therapy versus RE for advanced HCC is not currently available. It is therefore useful to: conduct a study using national data to establish the value of the resources used; take the specificities of local oncology practices into account; and compare sorafenib treatment to an up-to-date therapy, RE.

Limitations to the SARAH study design have been combated where feasible. While blinding is not possible due to the treatment methods, the potential biases caused by the lack of blinding have been minimised by the choice of OS as a robust primary endpoint. In addition, it is planned that an independent group of radiologists will perform a blind review of the imaging in order to guarantee the absence of bias regarding PFS.

The results from the SARAH trial should further the understanding of RE and determine the optimal treatment modality in advanced HCC. In addition, the data generated from this study may help to place RE into future consensus guidelines.

## Trial status

The SARAH trial is currently recruiting participants.

## Abbreviations

^99m^Tc: technetium-99 m
AASLD: American Association for the Study of Liver Diseases
ALT: alanine aminotransferase
AST: aspartate transaminase
CONSORT: Consolidated Standards of Reporting Trials
CT: computed tomography
DMC: Data Monitoring Committee
EASL: European Association for the Study of the Liver
ECOG: Eastern Cooperative Oncology Group
EORTC: European Organisation for Research and Treatment of Cancer
HCC: hepatocellular carcinoma
INR: international normalised ratio
ITT: intention to treat
NCI CTCAE: National Cancer Institute Common Terminology Criteria for Adverse Events
OS: overall survival
PFS: progression-free survival
QoL: quality of life
RE: radioembolisation
RECIST: response evaluation criteria in solid tumours
SARAH: SorAfenib versus Radioembolisation in Advanced Hepatocellular carcinoma
SHARP: Sorafenib Hepatocellular carcinoma Assessment Randomized Protocol
SIRT: selective internal radiation therapy
SPECT: single-photon emission computed tomography
TACE: transarterial chemoembolisation
ULN: upper limit of normal.
